# The immediate effect of traditional Malay massage on substance P, inflammatory mediators, pain scale and functional outcome among patients with low back pain: study protocol of a randomised controlled trial

**DOI:** 10.1186/s12906-016-0988-1

**Published:** 2016-01-15

**Keywords:** Low back pain, Massage, Substance P, Visual analogue pain scale, East Asian traditional medicine

## Abstract

**Background:**

The treatment of low back pain is very challenging due to the recurrent nature of the problem. It is believed that traditional Malay massage helps to relieve such back pain but there is a lack of scientific evidence to support both the practice of traditional Malay massage and the mechanism by which it exerts its effect. The aim of this study is to investigate the immediate effect of traditional Malay massage on the pain scale, substance P, inflammatory mediators, and functional outcomes among low back pain patients.

**Methods:**

A non-blinded, randomised controlled trial will be conducted. A total of sixty-six patients who fulfil the inclusion criteria will be recruited. The participants will be randomly allocated into intervention (traditional Malay massage) and control (relaxation position) groups. Blood and saliva samples will be collected before and immediately after intervention. All collected samples will be analysed. The primary outcomes are the changes in the level of substance P in both saliva and blood samples between both groups. The secondary outcomes include the levels of inflammatory mediators [i.e. TNF-α, IL-1β, IL-8, monocyte chemotactic protein-1, IL-6 and IL-10, and the soluble form of the intercellular adhesion molecule], the pain intensity as measured by a visual analogous scale and functional outcomes using the Roland-Morris Disability Questionnaire.

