The role of SP in the pathophysiology of clinical syndromes such as inflammatory joint disease and diseases with chronic neuropathic and inflammatory pain in general is becoming clearer [8]. There is a growing awareness that improved knowledge of SP may allow the development of drugs and interventions which target the modulation of SP so as to be able to help in treating the pain associated with these diseases. Many studies have used the level of SP in saliva as an indicator of the severity of pain in chronic pain conditions, since the amount of SP is significantly greater in saliva than in plasma. Also, the non-invasive nature of saliva collection suggests that SP in saliva may be useful as an alternative neurochemical correlation with chronic LBP [9–12].

Current analgesic therapy using non-steroidal anti-inflammatory drugs does not treat back pain effectively and, with long term use, is associated with kidney failure [13]. On the other hand, physical therapies, including massage and spinal manipulation, are known for their beneficial effect on pain reduction, and it has been suggested that this may be due to a reduction of the SP level in patients with LBP [12, 14]. The popularity of alternative medical treatment has increased for many conditions in recent years, and massage has been documented as one of the most frequently used alternative treatments for back pain [15].

The traditional Malay massage (TMM), known locally as “Urut Melayu”, involves deep friction and muscular massage of the whole body by the practitioner exclusively using their hands and fingers. It is culturally believed that this TMM healing is partially spiritual in nature [16, 17]. In the therapeutic aspect, TMM provides pain treatment as well as involvement of musculoskeletal problems such as muscle spasm. Other than that, it also helps in psychological aspects such as providing relaxation, improving confidence levels and reducing anxiety [17]. To date, ten government hospitals under the Ministry of Health, Malaysia offer TMM for the management of chronic pain under Traditional and Complementary Medicine units [18]. In 2011, 13,530 patients received TMM treatment in these units [19]. Although TMM is very popular, both in Malaysia but other countries in the Asian region [17], the acute and sustained effect of TMM on the aching muscle and its analgesic and anti-inflammatory mechanism remains unknown.

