### Outcome measures

The primary outcome measure for this study is the difference in the level of SP in blood and saliva samples pre- and post-intervention. All samples will be analysed at the Collaborative Drug Discovery Research (CDDR) Laboratory, Faculty of Pharmacy, UiTM Puncak Alam Campus.

The secondary outcome measures include the levels of inflammatory mediators [i.e., TNF-α, IL-1β, IL-8, monocyte chemotactic protein-1 (MCP-1), IL-6 and IL-10, and the soluble form of intercellular adhesion molecule (sICAM-1)] in both blood and saliva samples [20]. Other secondary outcome measures also include the visual analogous scale (VAS) score (indicating the pain intensity) and the Roland-Morris Disability Questionnaire (RMDQ) [21] score (assessing the level of disability associated with LBP).

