### Sample size calculation

The sample size is calculated using Power and Sample Size (PS) software 3.1.2 version [24]. The difference between the mean values of the intervention and control groups, and the standard deviation (post-massage) of SP levels were used as parameters for sample size calculation. Since there is no previous finding of the effect of TMM on substance P, we chose the closest related result based on traditional Thai massage on LBP patients reported by MacKawan et al. [12]. Their study reported that the mean levels of SP in the intervention group and control group are 50.43 pg/mL; 56.27 pg/mL, respectively (the difference in the mean values between the experimental and control groups is 5.84 pg/mL). Their findings also showed that the response within each subject group was normally distributed, with the highest recorded standard deviation being 8.3. The Type I error probability associated with this test of the null hypothesis is 0.05. A sample of 33 experimental subjects and 33 control subjects is therefore required to reject the null hypothesis that the population means of the experimental and control groups are equal, with a probability (power) of 0.8.

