### Data analysis plan

Data from participants will be entered into a computerised database and analysed using SPSS software version 20.0. The mean, standard deviation and range will be calculated for each variable. Data will be checked for a normal distribution in terms of skewness and kurtosis, normality test, univariate outliers and missing data. Data will be presented in table and line graphs. The paired *t*-test will be used to measure the differences pre- and post-intervention within and between groups for every outcome measure. A *p*-value of less than 0.05 will be used to show that the result is statistically significant.

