This is the first ever study conducted to quantify the pain and inflammatory mediators present before and after TMM. It must be noted, however, that MacKawan et al. [12] have previously investigated the effects of traditional Thai massage on SP and pain perception in patients with non-specific LBP. This type of Thai massage resembles TMM as it also emphasises deep friction using repetitive hands movement. Similar to our trial, their study was a randomized controlled trial in which the volunteers in the interventional arm were given 10 min of Thai massage. Their findings reported a significant decrease in the SP level in saliva after the Thai massage treatment [12]. This outcome was supported by Fields et al. who revealed that Swedish massage (a type of superficial massage) reduced the SP level [14]. Furthermore, the VAS pain score in the Thai massage group showed the presence of less pain than in the control group (Mean VAS score of 2.48 in the massage versus 3.36 in the control group). Meanwhile, another randomized controlled trial investigating the immediate effects of spinal manipulation on SP and pain perception on asymptomatic volunteers has been reported [29]. A total of 30 subjects were randomly assigned equally into three groups (control, cervical spine and dorsal spine manipulation). Unlike the study conducted using Thai massage [12], significant increases in SP levels immediately and 2 h after treatment were reported in the cervical manipulation groups. Furthermore, the pain pressure threshold level was elevated immediately after the spinal manipulation compared to the control group. Based on the results of their study, Molina-Ortega et al. postulated that the pain threshold level is increased when the SP increases. The caveats in these previous studies were that healthy volunteers were used to investigate the changes of SP post intervention and the control groups were exposure to certain degrees of manipulation and massage which could inadvertently have caused physiological changes.

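### Saliva and blood substance P are both primary, each tested at 0.05 with no success rule: depending on the rule, either the 5% error or the 80% power is lost, and power for blood is unknown

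*Protocol article*

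**What the plan says.** The Abstract (Methods) puts the two fluids on an equal footing: "The primary outcomes are the changes in the level of substance P in both saliva and blood samples between both groups". The Outcome measures section uses the singular but again covers both: "The primary outcome measure for this study is the difference in the level of SP in blood and saliva samples pre- and post-intervention". Under Instruments, the fluids are collected and assayed separately, so they yield two endpoints and not a composite.

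The Data analysis plan applies its t-test to every outcome measure and sets one threshold: "A *p*-value of less than 0.05 will be used to show that the result is statistically significant". The article contains no hierarchy, no split of alpha and no either/both rule.

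The Sample size calculation treats one null hypothesis: "The Type I error probability associated with this test of the null hypothesis is 0.05". Its inputs are one pair of means and one SD from a Thai massage trial: "Their study reported that the mean levels of SP in the intervention group and control group are 50.43 pg/mL; 56.27 pg/mL". The fluid is not named there. The Discussion reports that trial's SP finding as "a significant decrease in the SP level in saliva after the Thai massage treatment", and the Background states that "the amount of SP is significantly greater in saliva than in plasma". No planning mean or SD for blood SP appears anywhere.

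**The concern.** A trial with two primary outcomes needs a rule for what counts as success, and its alpha and sample size must fit that rule. Here the error rate and the power are stated for one test, but two primary tests will be run.

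The practical risk is a discordant result. If saliva SP is significant and blood SP is not, or the reverse, the plan does not say what the trial has shown, and the investigators could stress the favourable fluid after seeing the data. The Discussion reports that earlier studies disagreed even on the direction of the SP change after manual treatment, so agreement between the fluids cannot be taken for granted. It also expects the trial to supply the evidence for prescribing the massage, which calls for a primary question with one defined answer.

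**Working it through.** **Inputs from the Sample size calculation:** difference 56.27 − 50.43 = 5.84 pg/mL; SD 8.3; alpha 0.05 (sidedness not stated); power 0.8; 33 per arm.

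**Inputs assumed here:** the correlation ρ between the two test statistics (0 to 0.9) and, unless stated otherwise, the same standardised effect in blood as in the planning figures. The document gives neither.

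**1. The plan's own figure.** d = 5.84 / 8.3 = 0.704. The normal approximation gives n = 2(1.96 + 0.8416)² × 8.3² / 5.84² = 31.7, so 32 per arm. The exact two-sample t calculation, two-sided, gives 32.7, so 33 per arm, with power 80.4% at 33. One-sided versions give 25 or 26 and do not match. The stated 33 is therefore reproduced, for one comparison at two-sided 0.05.

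**2. Either fluid suffices, 0.05 each.** Family-wise error = 1 − P(|Z₁| < 1.96 and |Z₂| < 1.96), with Z₁ and Z₂ standard normal and correlation ρ. At ρ = 0 this is 1 − 0.95² = 0.0975.

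**3. Both fluids required, 0.05 each.** The type I error for the joint claim is at most 0.05. Joint power is the bivariate normal probability with each marginal at 0.804. At ρ = 0 it is 0.804² = 0.646.

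**4. Power for at least one fluid** = 2 × 0.804 − joint power.

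| ρ | Either: family-wise error | Either: power for at least one | Both: joint power |
|---|---|---|---|
| 0 | 9.75% | 96% | 65% |
| 0.5 | 9.1% | 92% | 69% |
| 0.7 | 8.3% | 89% | 72% |
| 0.9 | 7.0% | 85% | 75% |

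**5. If the effect in blood is smaller.** At 33 per arm and two-sided 0.05, power for blood alone is 22% at d = 0.3, 36% at 0.4, 52% at 0.5 and 67% at 0.6. Joint power cannot exceed these values. Under the either rule, power cannot fall below the 80.4% for saliva alone, provided the planning figures hold for saliva.

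**6. Alpha split, 0.025 each, 33 per arm.** Power per endpoint is 71%. Power for at least one fluid, with equal effects, is 92% (ρ = 0), 85% (0.5), 82% (0.7) and 77% (0.9).

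**The case against.** *The full protocol or analysis plan may hold the rule.* It may, and silence alone would not be a finding. But the article is not merely silent: it names two primary outcomes, fixes 0.05 for each, and gives a sample size valid for one comparison. Those three statements do not fit together as written.

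*A reader might infer that the 5% error and the 80% power are both lost.* The calculation does not support that. Under the either rule the error rises but power stays above 80%; under the both rule the error is controlled and the power falls. Only one fails at a time.

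*A reader might infer that no rule could deliver both.* That is also too strong. Splitting alpha goes with an at-least-one claim, for which the relevant power is 82% to 92% up to a correlation of 0.7 and 77% at 0.9, given equal effects; the 71% is power per endpoint. The article does not adopt this rule, but it is available with the same 66 patients.

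*A reader might infer that the saliva figures are shown not to apply to blood.* The Background says only that the amount of SP is higher in saliva than in plasma. A different level does not establish a different standardised effect. That the planning figures are salivary is itself a reasonable inference from the Discussion, not a statement in the Sample size calculation. What stands is that power for blood is unaddressed.

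*A reader might extend the point to the mediators, VAS and RMDQ, all held to the same 0.05.* These are labelled secondary. They do not change the error rate of the primary claim, and how they are adjusted is commonly left to the analysis plan.

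**Conclusion.** The point holds in a limited form. The sample size is right for one SP comparison, but the article declares two primary comparisons at 0.05 each without a success rule. Followed as written, it gives either a family-wise error of about 7.0% to 9.75% (correlation 0.9 to 0) with power kept, or an error of at most 5% with joint power of about 65% to 75% (correlation 0 to 0.9). The correlation is assumed, and the joint power also assumes that blood SP has the planning effect of 0.70. Power for blood SP is unknown; it would be 22% to 67% if its standardised effect were between 0.3 and 0.6, a range chosen for illustration.

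**What to change.** Choose one of two wordings before any outcome data are seen:

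- Name saliva SP as the single primary outcome, tested between groups at two-sided 0.05, with blood SP as key secondary.
- Or test in fixed order: saliva SP at two-sided 0.05, then blood SP at 0.05 only if saliva is significant. This holds the family-wise error at 5%.

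In either case, name the fluid in the Sample size calculation, state that the 80% power applies to saliva SP only, and bring the Abstract and the Outcome measures section into line. This presumes that the planning figures are salivary, which the investigators should confirm from the source trial.

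The sample size stays at 33 per arm, and the same samples are taken and reported. The cost is that blood SP loses equal primary status.

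If the investigators want both fluids required as co-primaries, 80% joint power needs 43 per arm at correlation 0, 41 at 0.5 or 37 at 0.9, and only if blood SP has an effect of 0.70. That route would first need a planning figure for blood.

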**Discussion:**

Massage is a type of physical therapy that has been proven to be potentially capable of reducing unpleasant pain sensations by a complex sensory response and chemical mediators such as substance P and various inflammatory mediators. Previous studies conducted using Thai, Swedish, or other forms of massage therapies, have showed inconsistent findings on substance P levels pre and post the interventions. Each massage genre varies in terms of massage and joint mobilization points, as well as the lumbar spinous process. Traditional Malay massage, known locally as “Urut Melayu”, involves soft-tissue manipulation of the whole body applied using the hands and fingers. This massage technique combines both deep muscular tissue massage and spiritual rituals. This trial is expected to give rise to new knowledge underlying the mechanisms for pain and inflammation relief that are activated by traditional Malay massage.

**Trial registration:**

Australian New Zealand Clinical Trials ACTRN12615000537550.

## Background

It has been reported that approximately 40–60 % Malaysians suffer from low back pain (LBP) [1]. A recent study by Hong et al. in the United Kingdom indicated that the total annual health care costs for patients with back pain were more than double than those of matched controls [2]. Pain is an unpleasant sensation, involving a complex sensory response due to tissue damage. The pain intensity varies from mild pain to severe pain sensations that require treatment. When there is cellular damage in the body, chemical mediators are released and detected by sensory neurons, resulting in the activation of pain receptors. There are many chemical mediators involved in periods of pain and inflammation, including substance P (SP).

SP is a neuropeptide produced in a subset of capsaicin sensitive sensory peripheral neuron cell bodies localised in dorsal root and trigeminal ganglia, which plays a pivotal role in the transmission of noxious stimuli in the spinal cord [3]. Structurally, SP is an 11-amino acid polypeptide whose C-terminal amino acid sequence is essential for its pharmacological activities. It preferentially binds to the neurokinin 1 (NK1) receptor. After binding to this receptor, SP modifies Ca^2+^ and K^+^currents at the cellular level [3]. The role of SP in the onset of pain and inflammation is being increasingly recognised [4, 5]. The physiology involved in the initiation of and response to muscle pain is associated with activation of the group C afferent nerve fibres and is usually accompanied by a certain degree of tissue damage. This in turn results in the release of chemical mediators, including SP, from the damaged cells and the activation of nociceptor nerve endings. These chemical mediators, especially SP, sensitize the nociceptors’ response to normal stimuli by altering the transduction properties of the free nerve endings [6, 7].

The role of SP in the pathophysiology of clinical syndromes such as inflammatory joint disease and diseases with chronic neuropathic and inflammatory pain in general is becoming clearer [8]. There is a growing awareness that improved knowledge of SP may allow the development of drugs and interventions which target the modulation of SP so as to be able to help in treating the pain associated with these diseases. Many studies have used the level of SP in saliva as an indicator of the severity of pain in chronic pain conditions, since the amount of SP is significantly greater in saliva than in plasma. Also, the non-invasive nature of saliva collection suggests that SP in saliva may be useful as an alternative neurochemical correlation with chronic LBP [9–12].

Current analgesic therapy using non-steroidal anti-inflammatory drugs does not treat back pain effectively and, with long term use, is associated with kidney failure [13]. On the other hand, physical therapies, including massage and spinal manipulation, are known for their beneficial effect on pain reduction, and it has been suggested that this may be due to a reduction of the SP level in patients with LBP [12, 14]. The popularity of alternative medical treatment has increased for many conditions in recent years, and massage has been documented as one of the most frequently used alternative treatments for back pain [15].

The traditional Malay massage (TMM), known locally as “Urut Melayu”, involves deep friction and muscular massage of the whole body by the practitioner exclusively using their hands and fingers. It is culturally believed that this TMM healing is partially spiritual in nature [16, 17]. In the therapeutic aspect, TMM provides pain treatment as well as involvement of musculoskeletal problems such as muscle spasm. Other than that, it also helps in psychological aspects such as providing relaxation, improving confidence levels and reducing anxiety [17]. To date, ten government hospitals under the Ministry of Health, Malaysia offer TMM for the management of chronic pain under Traditional and Complementary Medicine units [18]. In 2011, 13,530 patients received TMM treatment in these units [19]. Although TMM is very popular, both in Malaysia but other countries in the Asian region [17], the acute and sustained effect of TMM on the aching muscle and its analgesic and anti-inflammatory mechanism remains unknown.

There is a lack of scientific evidence, however, to support the practice of TMM and the mechanism by which it reduces back pain. It has been postulated that there is a link between the positive effect of TMM and the presence of SP in patients with LBP [12]. The aim of this study, therefore, is to investigate the immediate effect of TMM on SP, inflammatory mediators, pain intensity and quality of life among LBP patients. The results of this research will be instrumental in elucidating the value of TMM in human pathology.

## Methods

### Study design

A non-blinded, 2-arm randomized controlled trial will be conducted. A total of 66 eligible participants will be randomly assigned into two groups: (i) TMM or (ii) control groups, using a simple random sampling method. Random allocation to either the intervention or control group is achieved by sequentially numbered, sealed opaque envelopes containing the group allocation, which will be determined by a computer-generated random number. A research assistant with no direct contact with the participants will be responsible for generating the random numbers and preparing the envelopes. Ethical approval has been obtained from the UiTM Research Ethics Committee [600-RMI(5/1/6)].

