### Instruments

Both blood and saliva samples will be collected and centrifuged (10,000 g and 4 °C for 15 min) to eliminate debris and cellular matter. Then, the Human Substance P EIA kit (Cusabio Biotech; CSB-E08357h) will be used to determine the level of SP. Other inflammatory mediators, such as TNF-α (eBioscience; BMS2034TEN), IL-1β (Cayman chemical;583311-96 well), IL-6 (BMS213/2TEN), IL-8 (eBioscience; BMS204/3), IL-10 (eBioscience; BMS215/2), monocyte chemotactic protein-1(MCP-1) (eBioscience; BMS281) and the soluble form of the intercellular adhesion molecule (sICAM-1) (Arigo; ARG80215), will be tested individually in both blood and saliva samples using a human Elisa kit (Table 1).

**Table 1 Tab1:** Analytical and assessment characteristics

No.	Assessment	Explanation
1.	Blood sample	Blood collection
		- 10 ml of venous blood will be taken by a trained nurse.
		- The whole blood will be collected into a plain polyethylene tube until blood clot formation.
		- The clots will be separated from the wall of tube using a wooden applicator stick.
		- The serum will be separated by centrifugation at 10,000 g at 4 °C for 15 min to eliminate debris and cellular matter.
		Blood test
		1) Substance P
		- The blood serum will be tested using Human Substance P EIA kit (Cusabio Biotech)
		2) Cytokines
		- The blood serum will be tested individually using Elisa kits to investigate
		a) TNF-α
		b) IL-1β
		c) IL-6
		d) IL-8
		e) IL-10
		c) monocyte chemotactic protein-1 (MCP-1)
		d) The soluble form of intercellular adhesion molecule (Sicam-1).
2.	Saliva sample	Saliva collection
		- 3 to 4 ml of unstimulated (resting) whole saliva will be collected 2 min after the patient has rinsed his/hermouth several times with tap water.
		- The accumulated saliva in the floor of the mouth will be drawn by a plastic disposable pipette and collected into a plastic polyethylene tube.
		- The collected saliva will be centrifuged at 10,000 g at 4 °C for 15 min to eliminate debris and cellular matter.
		Blood test
		1) Substance P
		- The blood serum will be tested using Human Substance P EIA kit (Cusabio Biotech)
		2) Cytokines
		- The blood serum will be tested individually using Elisa kits to investigate:
		a) TNF-α
		b) IL-1β
		c) IL-6
		d) IL-8
		e) IL-10
		c) monocyte chemotactic protein-1 (MCP-1)
		d) The soluble form of intercellular adhesion molecule (sICAM-1).

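### The trial is declared non-blinded without exception, although the substance P assay and the cleaning of its data could be masked to arm and time point

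*Protocol article*

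**What the plan says.** The blinding status is given twice in the protocol article, each time without qualification: "A non-blinded, randomised controlled trial will be conducted" in the Abstract and "A non-blinded, 2-arm randomized controlled trial will be conducted" under Study design.

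Outcome measures defines the primary outcome: "The primary outcome measure for this study is the difference in the level of SP in blood and saliva samples pre- and post-intervention". The same section places the measurement in a laboratory: "All samples will be analysed at the Collaborative Drug Discovery Research (CDDR) Laboratory, Faculty of Pharmacy, UiTM Puncak Alam Campus". Instruments names the assay: "the Human Substance P EIA kit (Cusabio Biotech; CSB-E08357h) will be used to determine the level of SP".

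The Data analysis plan adds a checking step: "Data will be checked for a normal distribution in terms of skewness and kurtosis, normality test, univariate outliers and missing data". It does not say what is done with a flagged value, or whether the person who decides knows the arm.

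The only separation of roles described concerns allocation: "A research assistant with no direct contact with the participants will be responsible for generating the random numbers and preparing the envelopes".

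**The concern.** One arm receives massage and the other a relaxation position, so neither the participants nor the practitioner can be masked. The self-reported pain and disability scores are therefore open as well. Substance P is different. It is measured in tubes, away from the participant, and the people who run the assay and clean the data need not know which arm or time point a tube came from.

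The optical reading is made by an instrument, but people decide whether a sample is run again and whether an extreme value is kept. If they know the arm, their decisions can lean in one direction without anyone intending it. In an otherwise open trial, the primary outcome is where masking is practicable, and the declared design does not claim it.

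**Working it through.** **1. The passages side by side**

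- Study design and Abstract: non-blinded, with no role exempted.
- Outcome measures and Instruments: the primary outcome is a kit assay run in a laboratory.
- Data analysis plan: a check for outliers, with no handling rule and no masking stated.
- Study design: the envelope procedure protects allocation. It does nothing for measurement or cleaning.

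The reason for an open design covers participants and practitioner. It does not cover the assay, re-runs, outlier decisions or analysis.

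**2. The plan's own figure**

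Inputs from Sample size calculation: means 50.43 and 56.27 pg/mL, difference 5.84, SD 8.3, alpha 0.05, power 0.8, 33 per arm. The number of sides is not stated.

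- Normal approximation, two-sided: n = 2 × (1.960 + 0.842)² × (8.3 / 5.84)² = 31.7, so 32 per arm.
- Two-sample t-test, two-sided: 32.7, so 33 per arm, with power 0.804 at 33. The stated figure is reproduced.
- A one-sided calculation gives 25 per arm and does not match.

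Masking the assay changes none of these inputs.

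**3. The planned effect in context**

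- Relative to the control mean: 5.84 / 56.27 = 10.4%.
- Standard error of the difference: 8.3 × √(2/33) = 2.04 pg/mL.
- Smallest difference reaching p < 0.05: about 2.00 × 2.04 = 4.1 pg/mL.

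**4. Illustration: two values dropped from one arm**

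Assume two values, each 2 SD (2 × 8.3 = 16.6 pg/mL) above the mean of their arm, are dropped from that arm and none from the other.

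- Shift of the mean: 2 × 16.6 / 31 = 1.07 pg/mL.
- Relative to the planned effect: 1.07 / 5.84 = 18%.

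**5. Illustration: effect on type I error**

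Assume no true difference, SD 8.3, 33 per arm, and a shift b between arms that comes only from handling. The noncentrality is b / 2.04 with 64 degrees of freedom.

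| Assumed shift b (pg/mL) | Two-sided type I error |
|---|---|
| 0 | 5.0% |
| 0.5 | 5.7% |
| 1 | 7.7% |
| 2 | 16.1% |
| 3 | 30.4% |

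The shift sizes are assumptions; the document gives none.

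**The case against.** The strongest reply is that this is a condensed article. Tube labels, plate layout and re-assay rules usually sit in a laboratory manual or analysis plan, and non-blinded may be only a general label for unmasked participants and practitioner. A kit read-out is also less exposed to observer bias than the self-reported scores, which masking the laboratory would not protect.

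Much of this stands, and it rules out several stronger readings:

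- **That laboratory staff will know the arm.** A reader might infer this from the label, but no section says so. The article names the laboratory and does not describe how tubes are marked.
- **That outliers will be removed.** The Data analysis plan provides for a check. Removal is one possible consequence and is not planned in the text, so the 1.1 pg/mL figure is a one-sided illustration.
- **That plate differences create a bias as large as the effect.** An assumed plate shift of 5–15% would be 2.8–8.4 pg/mL (0.05 and 0.15 × 56.27) if the arms sat on different plates. Neither the percentage nor such a layout is in the document. Plate confounding is also separate from masking: unmasked staff can balance plates and masked staff can fail to. A plate shift between time points that is common to both arms cancels when changes are compared between arms.
- **That masking costs nothing.** Coding, storing and batching samples takes some work.

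The reply does not remove the point, because the point rests on a stated design choice and not on missing laboratory detail. If samples are in fact coded, the unqualified statement is inaccurate and should be corrected. If they are not, an avoidable risk to the primary outcome remains.

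**Conclusion.** The point holds as a weakness in the declared design. The article calls the trial non-blinded with no exception, although only participants and practitioner need be open and the primary outcome can be assayed and cleaned masked. As declared, re-assay decisions and decisions on flagged values may be made with knowledge of the arm.

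The document does not allow the size of the resulting bias to be derived, and it does not show that any bias will occur. The illustrations show only that modest handling differences matter against an effect of this size, and they rest on the assumed shifts, an SD of 8.3 and 33 per arm. This should be changed before the assays are run, because masking cannot be added to decisions already taken.

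**What to change.** - Reword the design statement along these lines: open to participants and practitioner; laboratory staff and data analyst masked.
- Label tubes with neutral codes that hide both arm and time point.
- Have the research assistant who already generates the allocation hold the code. This needs no additional staff.
- Settle all re-assay and outlier decisions, and record them, before the code is broken.

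Keeping each participant's pre and post samples on one plate, with the arms balanced across plates, is a sensible accompanying step, but it is a separate laboratory detail. The code holder would have to draw up that layout.

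The cost is a small effort for coding, storage and batching of samples. Sample size, alpha, power, visits and treatment do not change.
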